# Statistical Analysis

## General principles

**Analysis data**: Women who fall in the [exclusion criteria](#inclusion_exclusion_criteria) will be excluded from all analyses.

**Quantifying uncertainty:** Unless stated otherwise all p-values will be two-sided, and 95% confidence intervals used. There will be no adjustment for multiple testing unless specified.

**Missing data**: Primary analysis will include all women within the inclusion criteria and with complete data on primary endpoint. Details for dealing with missingness when deriving variable are in [section 3.2.2.](#derived_variables)

Overall, very low level of missingness is expected for any variable. In case of missingness on source data, all enquires will be first consulted with data team of the programme, to check whether this can be completed. If the problem cannot be solved, data imputation will be used for a variable, only if the missingness exceeds 80 screenees (5% of the total expected study participants).

**Reporting:** Statistical significance will be assessed at the two-sided 5% level unless otherwise stated. 95% confidence intervals will be provided as appropriate.

**Software**: The data management and analysis will be carried out using computer programme STATA version 17.0^6^.

## Primary analysis

For the primary analysis a hierarchical approach will be used for testing at the 5% level. In the first instance, a global likelihood ratio test on 3 degrees of freedom will be applied to assess the significance of a difference in any direction among the groups overall. Also, a four-way comparison with OO as the reference category.

To account for multiple comparisons, null hypotheses (no difference in 90-day screening attendance between arms) will be tested in the following order:

(1) Timed Timed (TT) vs Open Open (OO).

(2) TT vs OT.

(3) TO vs OT.

(4) TT vs TO.

(5) OT vs OO.

Testing will only proceed if the preceding hypothesis was rejected at the 5% level (p-value <0.05).

Independently of significance test results, both overall and for specific subgroups, we will report the most successful group in terms of 90-day attendance.

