## Primary endpoint methods

For the primary endpoint, Poisson regression will be used, with number of subjects attending within 90 days of their first offered appointment as the outcome (*90dayattend)*, offset by total numbers invited.

The attendance rate within 90 days of the first offered appointment in the study arms is compared using Poisson regression model with robust variance estimates to take account of clustering in the allocation to arms OI and TA at the first invitation^7^. In STATA the command **poisson** with option **vce(robust)** is used, reporting with 95% confidence interval using **level (95)**, and with option **irr** to output estimated coefficient as incidence-rate ratios.

A likelihood-ratio test is used to check the significance of the regression coefficient in the poisson regression model (STATA **lrtest**). Statistical testing will be two-sided, with p<0.05 considered to be statistically significant. We will compare each of the other groups with the OO group as reference category. Thereafter pairwise comparisons will be carried out as described above. We conclude the following for

- IRR < 1, the attendance rate is decreased for the considered study arm compared to the reference category.
- IRR = 1, no difference between the attendance rate of the considered study arm and the reference category.
- IRR > 1, the attendance rate is increased for the considered study arm compared to the reference category.

The IRR is significantly greater or smaller than 1, if 1 is not within the border of the 95% CI, which is analogue to the p-value is smaller than 0.05.

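### Comparisons of each arm with OO sit outside the ordered list but can still be called significant, so OT vs OO and TO vs OO can bypass the 5% gate (familywise error up to about 12%)

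*SAP*

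**What the plan says.** The SAP's Primary analysis section opens: "For the primary analysis a hierarchical approach will be used for testing at the 5% level". It then lays out three things.

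- A global test: "In the first instance, a global likelihood ratio test on 3 degrees of freedom will be applied". The section does not say whether later tests depend on its result.
- The comparisons with OO: "Also, a four-way comparison with OO as the reference category". No condition is attached.
- The ordered list, with its purpose: "To account for multiple comparisons, null hypotheses (no difference in 90-day screening attendance between arms) will be tested in the following order". The order is TT vs OO, TT vs OT, TO vs OT, TT vs TO, OT vs OO. The stopping rule is "Testing will only proceed if the preceding hypothesis was rejected at the 5% level (p-value <0.05". TO vs OO is not in the list.

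The Primary endpoint methods section returns to the second item: "We will compare each of the other groups with the OO group as reference category". It places the listed pairwise tests after that. It gives two significance rules: "Statistical testing will be two-sided, with p<0.05 considered to be statistically significant" and "The IRR is significantly greater or smaller than 1, if 1 is not within the border of the 95% CI". Neither is limited to contrasts reached in the sequence. The General principles section rules out multiplicity adjustment except where specified, and none is specified for the comparisons with OO.

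The Table 4 template has five numbered rows, one for each listed contrast, with a p-value column for 90-day attendance. It has no row for TO vs OO.

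**The concern.** A fixed sequence controls the familywise error only if significance claims are made through it. Here three comparisons with OO stand beside it, each judged at an unadjusted 5%. TT vs OO is also step 1 of the list, so it is tested at 5% in any case. OT vs OO is step 5, yet under the CI rule it could be declared significant after the sequence had stopped at step 2. TO vs OO has no gated test at all.

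Both contrasts bear on policy. The Introduction says that open invitations are planned as standard from 2024/25, and these contrasts ask whether adding one timed letter improves on an all-open approach. A claim on either would carry the authority of the primary analysis without the protection the plan says it has.

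**Working it through.** **Inputs.** Two-sided 5% per test (Primary analysis; Primary endpoint methods). Planned arms of 4,000, and rates of 65% and 73% (Sample Size Justification). Equal arms give a correlation of 0.5 between two comparisons that share OO.

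**The plan's own figures.** The stated 524 per group is reproduced:

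n = [1.960·√(2·0.69·0.31) + 0.842·√(0.65·0.35 + 0.73·0.27)]² / 0.08² = (1.282 + 0.548)² / 0.0064 ≈ 523.5, rounded up to 524.

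At 4,000 per arm, power for the same difference exceeds 99.99%. A true difference of that size is therefore treated below as always detected, so the sequence always moves past it. The 5% level is also reproduced for the list on its own: 5.0% in all seven true patterns simulated (2,000,000 replicates each).

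**Adding the ungated comparisons with OO.** In each true pattern, only contrasts between equal arms can give a false claim. The critical value is c = 1.96.

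1. *All arms equal.* The three comparisons with OO are all true nulls, and step 1 is one of them, so the list adds nothing further. With k comparisons sharing a control, the error is 1 − ∫ φ(x)[Φ(x + c√2) − Φ(x − c√2)]^k dx. For k = 3 this is 12.54%. Simulations, including a binomial one at 4,000 per arm with robust log-ratio tests, gave 12.4% to 12.6%.
2. *Only TT differs.* Steps 1 and 2 pass. TO vs OT (step 3), OT vs OO and TO vs OO are then each tested at 5%. These are all the pairs among three equal arms, so the error is the chance that the range of three standard normals exceeds 1.96·√2, which is 12.2%.
3. *Only the first letter matters* (TT = TO, OT = OO). The true nulls tested are TT vs TO (step 4) and OT vs OO (ungated). They share no arm, so the error is 1 − 0.95² = 9.75%.
4. *Only the second letter matters* (TT = OT, TO = OO). The true nulls are TT vs OT (step 2) and TO vs OO (ungated), again 9.75%.
5. *Only TO, or only OT, differs.* Two ungated true nulls share OO. The formula with k = 2 gives 9.1%.
6. *Only OO differs.* No comparison with OO is a true null, so only the list can err: 5.0%.

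| True pattern | List alone | List plus OO comparisons | Same, all gated by the global test |
|---|---|---|---|
| All equal | 5.0% | 12.5% | 4.0% |
| Only TT differs | 5.0% | 12.2% | 12.2% |
| Only first or only second letter matters | 5.0% | 9.75% | 9.75% |
| Only TO or only OT differs | 5.0% | 9.1% | 9.1% |
| Only OO differs | 5.0% | 5.0% | 5.0% |

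The last column follows because a 3-df global test is almost certain to reject once one arm truly differs, and then protects nothing behind it.

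**Which p-value.** The figures need tests of true 5% size, as intended for the robust CI. A plain Poisson likelihood-ratio test on a yes/no outcome assumes too large a variance. The true variance is 1 − 0.65 = 0.35 of the assumed one, so the effective critical value is 1.96/√0.35 = 3.31. That gives about 0.09% per test and about 0.3% for any of three.

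**After the fix.** With significance confined to the list and TO vs OO appended as step 6, the familywise error is 5.0% in all seven patterns.

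**The case against.** The strongest defence is that the comparisons with OO were only ever the parameterisation of one Poisson model. Table 4 supports this: it plans p-values for exactly the five listed contrasts and has no second set referenced to OO. This has weight, and a reader who infers that the OO comparisons cannot be descriptive goes too far. But nothing in the text calls them descriptive, and the CI rule in Primary endpoint methods covers every ratio without exception.

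Second, the announced hierarchy puts the global test first, so it may be meant as a gate. That is a fair reading. It brings the all-equal case down to 4.0% but changes no other row of the table.

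Third, the pattern in which only TT differs is unlikely, since each timed letter would have to do nothing without the other. The SAP's background expects timed letters to help. If each letter helps, all three arms differ from OO and only the list can err, at no more than 5%. This stands for the scenario the study was built around. Control of the familywise error must nevertheless hold whatever the truth, and the patterns in which only one letter matters (9.75%) are not far-fetched.

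Fourth, the likelihood-ratio route would be very conservative. This is true, but the CI rule lets the robust interval decide.

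Two further inferences are not supported. TT vs OO appearing twice adds no error, because step 1 is always tested at 5%. Leaving TO vs OO out of the list is not a fault in itself: a fixed sequence need not contain all six pairs, and the Secondary analysis section compares first-letter strategies separately, with a Bonferroni correction.

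**Conclusion.** The concern holds as a gap in the wording around a sound ordered list. As written, OT vs OO and TO vs OO can be declared significant without passing the gate that is there to account for multiple comparisons.

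A reader might infer that the primary error rate simply is about 12%. The document does not support that. About 12% is the worst case, and the rate ranges from 5.0% to 12.5% over the patterns examined. It rests on three assumptions: tests of true 5% size, equal arms, and true differences large enough to be detected almost always. It also takes the CI rule at its word for the ungated ratios. If the sponsor meant those ratios as estimates only, the 5% level is intact, but the SAP has to say so.

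**What to change.** - In Primary analysis and Primary endpoint methods, state that significance is claimed only for contrasts reached in the ordered list.
- Restrict the CI-excludes-1 rule to those contrasts.
- Describe the OO-referenced ratios otherwise as descriptive estimates with 95% CIs and no p-values.
- If a test of TO vs OO is wanted, append it as step 6, with a matching row in Table 4, only if this is done before outcome data are seen. The list of changes records analysis running to 3 May 2024, and the supplementary material already discusses attendance by strategy. If outcomes have been seen, an added step would be post hoc, and TO vs OO should be reported descriptively.

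The cost is a few sentences and at most one table row, with no new data or modelling. The downside is small: fewer contrasts can be called significant if the sequence stops early.

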# Introduction

Attendance in the UK NHS Breast Screening Programme has previously exceeded 70% on average. In the past, women initially received a timed appointment as their first invitation, followed by either a 2^nd^ timed appointment or an open invitation for women who did not attend their first appointment. Previous work showed that a second timed appointment letter was effective at improving screening participation^1^. However, during the Covid pandemic open invitation letters were used routinely to help the screening services to recover more quickly^2^. With the NHS breast screening services (NHSBSP) moving to a new IT system, open invitation letters with online and phone booking are planned to be used as standard from 2024/25.

This study has been commissioned to evaluate the effect of different combinations of timed appointments and open invitations on attendance rate at the NHS Breast Screening Programme. Below describes the statistical analysis plan for the evaluation of the effect of different strategies, either timed or open appointments, for the first invitation, or second invitation for non-attenders.

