## Sample Size Justification

We aimed for a sample size of 16,000 women for the following reasons.

Previous results comparing timed to open invitations suggest an absolute 8% increase in participation with timed appointments compared to open invitations. As noted above, there is an interest in subgroup analyses. For a comparison of two groups with participation rates of 65% and 73%, 524 persons per group would give 80% power to detect this difference as significant at 5% level with two-sided testing. To allow for estimation of the primary outcome in socioeconomic and ethnic subgroups, we planned to evaluate 16,000 women in total (4,000 per arm).

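### The fixed testing order makes TT vs TO and OT vs OO wait for TO vs OT, a contrast that is null when both letters work equally well, so whether they are tested turns on an effect split the SAP does not state

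*SAP*

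**What the plan says.** SAP, Primary analysis, introduces the order as the multiplicity control: "To account for multiple comparisons, null hypotheses (no difference in 90-day screening attendance between arms) will be tested in the following order". The order is (1) TT vs OO, (2) TT vs OT, (3) TO vs OT, (4) TT vs TO, (5) OT vs OO. The stopping rule follows: "Testing will only proceed if the preceding hypothesis was rejected at the 5% level (p-value <0.05".

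SAP, Sample Size Justification, rests on one two-group comparison: "For a comparison of two groups with participation rates of 65% and 73%, 524 persons per group would give 80% power", two-sided at 5%. The 8 points come from earlier timed-versus-open results: "Previous results comparing timed to open invitations suggest an absolute 8% increase in participation with timed appointments compared to open invitations". The section does not say which of the four arms carry 65% and 73%, or how the 8 points divide between the first and second letter. The planned size is 16,000 women, 4,000 per arm.

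The Introduction says of the second letter: "Previous work showed that a second timed appointment letter was effective at improving screening participation". It also makes clear that this letter goes only to women who did not attend after the first.

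SAP, Secondary analysis, separately compares (TT+OT) with (TO+OO), Bonferroni corrected. That test is not made conditional on any step of the primary sequence.

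**The concern.** A fixed sequence works well when each gate is at least as likely to be rejected as the hypotheses behind it. Here the third gate moves against the hypotheses it guards. The larger the second-letter effect, up to equality with the first-letter effect, the smaller the TO vs OT difference. TT vs TO and OT vs OO can therefore be real and well powered, yet never formally tested because two single-timed strategies turned out similar.

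At stake are two of the five primary hypotheses: whether a timed second letter adds attendance after a timed first letter, and whether it does so after an open one. Their estimates and intervals would still appear in Table 4, but without a confirmatory test.

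**Working it through.** **Inputs.** From the SAP: 65% and 73%, two-sided 5%, 4,000 per arm, the five-step order and its gate. Assumed, because the SAP is silent: which arms carry 73% and 65%, and how the 8 points split.

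**The plan's own figure.** With pooled variance and mean rate 0.69:
n = [1.960·√(2·0.69·0.31) + 0.8416·√(0.65·0.35 + 0.73·0.27)]² / 0.08² = (1.2819 + 0.5484)² / 0.0064 = 523.5, so 524 per group. The stated figure is reproduced. It describes a single ungated test.

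**What each step tests.** Let a be the first-letter effect and b the second-letter effect, in points over all invited women and additive. Then TT − OO = a + b (step 1), TT − OT = a (step 2), TO − OT = a − b (step 3), TT − TO = OT − OO = b (steps 4 and 5). Step 3 is null when a = b. Step 2 is null when a = 0.

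**Check by formula.**
- 4+4: TO = OT = 69%, so step 3 is rejected only 5% of the time. TT vs TO as a single test: SE = √[(0.73·0.27 + 0.69·0.31)/4000] = 0.01014, z = 0.04/0.01014 = 3.95, power = Φ(3.95 − 1.96) = 98%.
- 5+3: TO = 70%, OT = 68%, SE = √[(0.70·0.30 + 0.68·0.32)/4000] = 0.01034, z = 1.93, power of step 3 = Φ(1.93 − 1.96) = 49%.

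**Simulation.** 200,000 trials per row, Wald tests on the log ratio with binomial variance, TT = 73%, OO = 65%. Each pair of columns to the right gives power for TT vs TO / OT vs OO.

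| Split a+b | Step 4 reached | Single tests | Written sequence | TT vs OO, then Holm |
|---|---|---|---|---|
| 6+2 | 97% | 51%/47% | 49%/22% | 44%/40% |
| 5.5+2.5 | 83% | 70%/66% | 54%/32% | 63%/59% |
| 5+3 | 49% | 84%/81% | 36%/25% | 79%/75% |
| 4+4 | about 4.5% | 98%/97% | 4%/4% | 95%/94% |
| 3+5 | 37% | 100%/100% | 36%/36% | 99%/99% |
| 2+6 | 49% | 100%/100% | 49%/49% | 100%/100% |

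At 7+1, step 4 is reached in over 99% of trials. At 6+2, the drop in OT vs OO comes mainly from waiting for TT vs TO, not from step 3. At 2+6, the block is at step 2.

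**If the 8 points are the first-letter effect alone (a = 8).** Step 4 is reached in over 99% of trials at b = 3, 97–98% at b = 4, 81–85% at b = 5 and 47–51% at b = 6. Each range covers setting TT or TO at 73%. Step 3 then rarely blocks for b up to about 4 points.

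**Pooled second-letter contrast.** Taking Bonferroni as 0.025 for each of two contrasts (an assumption), power is 69% at 6+2, 97% at 5+3 and over 99% at 4+4.

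**The case against.** A reader might infer that under the sizing rates of 73% and 65% the second-letter hypotheses would usually go untested. The SAP does not support that. It assigns those rates to no pair of arms and gives no split. If the first letter carries 5.5 of the 8 points or more, step 4 is reached in 83% to over 99% of trials. If the 8 points are the first-letter effect alone, step 3 is a minor obstacle.

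The second letter also reaches only non-attenders, so a smaller b than a is plausible, and the written order suits an expected ranking of TT, TO, OT, OO. This stands as a reason to call the loss conditional, but it does not remove it. Suppose each timed letter adds the same 8 points among those who receive it, open first-letter attendance is 50%, and open second-letter attendance is 20% (all assumptions). Then OO, OT, TO and TT are 60.0%, 64.0%, 66.4% and 69.8%, and TT vs TO falls from 90% as a single test to 52% in sequence.

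A reader might also infer that no formal test of the second letter would remain. That is wrong too: the pooled contrast is outside the sequence and is strongest where step 3 blocks most. It averages over the first letter, however, and cannot stand in for either pairwise hypothesis.

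Finally, TO vs OT is a legitimate strategy question, and Holm exchanges power rather than only adding it. Both points are fair. But TO = OT and TT = TO together imply TT = OT. Once TT vs OT is rejected, at most one of the two can be a true null, so making TT vs TO wait for TO vs OT buys no error control.

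**Conclusion.** The point holds in conditional form. The written sequence controls the family error rate, but it makes two primary hypotheses depend on a contrast whose size is set by an unstated split. With TT 73%, OO 65% and 4,000 per arm, the cost for TT vs TO / OT vs OO runs from almost the whole power at 4+4 (98%/97% to 4%/4%), through 84%/81% to 36%/25% at 5+3, to 2 points for TT vs TO and 25 for OT vs OO at 6+2. Only the pairwise primary tests are affected; Table 4 estimates and the pooled secondary contrast remain.

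The figures assume additive effects, equal arms of the planned size and independent women. The SAP mentions clustering in the allocation but gives no size for it; clustering would lower all these powers. The preliminary global test was not simulated as a gate.

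**What to change.** **Preferred.** In SAP, Primary analysis, keep TT vs OO as the gate at two-sided 5%. If it is rejected, test TT vs OT, TO vs OT, TT vs TO and OT vs OO together by Holm's procedure at two-sided 5%. Family error stays at 5%: if TT = OO the gate limits it, otherwise Holm does. Results for the second-letter tests are in the last column of the table. The cost is a sentence of wording, no new data, and up to about 7 points of power on TT vs TO or TO vs OT when the first letter dominates (TT vs TO 49% to 44% at 6+2, 51% to 44% at a = 8, b = 2 with TT at 73%; TO vs OT 49% to 43% at 5+3).

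**No-cost minimum.** Keep the order, but once TT vs OO and TT vs OT are rejected, test TO vs OT and TT vs TO each at 5% with neither gating the other. Test OT vs OO only if both are rejected. Family error stays at 5% by the implication given above, and no comparison loses power. TT vs TO rises to 96% at 4+4 and 84% at 5+3. OT vs OO gains nothing, and the block at TT vs OT remains when the first-letter effect is small.

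Either way, state in Sample Size Justification which arms the 65% and 73% refer to and what split between letters is expected.

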## Secondary analysis

For the secondary analysis, we will use hierarchical approach to compare attendance for the two invitation strategies for

1. the first invite (TT+TO) vs (OT+OO) and
2. the second invite (TT+OT) vs (TO+OO).

Effect sizes will be presented with 95%CIs and p-value (Bonferroni corrected).

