## Design

To meet these objectives, an evaluation was run to compare four strategies:

1. Timed for both first and second invitation (TT),
2. Open invitations for both (OO),
3. Timed followed by Open invitation (TO), and
4. Open followed by Timed invitations (OT).

Women were allocated to each strategy based on whether certain digits in their screening identifier (SX) and NHS number were even or odd (quasi-randomisation as shown in figure 1 of the evaluation protocol for randomisation procedure).

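### The second-letter effect is planned only on all invited women; a supplementary analysis among first-letter non-attenders would recover more than half of the information at little cost

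*SAP*

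**What the plan says.** The SAP's Introduction describes the strategies under study as "either timed or open appointments, for the first invitation, or second invitation for non-attenders". A woman who attends after her first letter therefore has no second letter to receive.

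Design explains the allocation: "Women were allocated to each strategy based on whether certain digits in their screening identifier (SX) and NHS number were even or odd". The Data dictionary lists two separate odd/even fields, one from each identifier, and the Figure 1 template shows a first-letter and a second-letter allocation stage.

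Secondary analysis sets the contrast for "the second invite (TT+OT) vs (TO+OO") and adds: "Effect sizes will be presented with 95%CIs and p-value (Bonferroni corrected"). It names no denominator of its own. Primary endpoint methods does, in specifying the Poisson model as "offset by total numbers invited", and the Table 5 template has one IRR per contrast with no row for non-attenders. Primary analysis lists TT vs TO fourth and OT vs OO fifth in its fixed testing order; each pair differs only in the second letter.

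Sample Size Justification works from a single timed-vs-open difference of 8 points. It states that "524 persons per group would give 80% power to detect this difference as significant at 5% level with two-sided testing", and then "we planned to evaluate 16,000 women in total (4,000 per arm"). No second-letter effect is sized, and no analysis restricted to first-letter non-attenders is described.

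**The concern.** Within a first-letter type, women who attend on the first letter are alike in both second-letter groups by design. They tell us nothing about the second letter, but they stay in numerator and denominator, add variance and pull the ratio towards 1. A worthwhile gain among the women who actually face the second letter can therefore show up as an IRR of about 1.03 with a confidence interval that includes 1.

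The choice of second letter is a decision about non-attenders, and the report would hold no estimate for them. The testing order adds to this: if TT vs TO is not rejected at step four, OT vs OO is not formally tested.

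**Working it through.** **The plan's own figure.** For 65% vs 73%, two-sided 5%, 80% power, with pooled variance under the null and no continuity correction:

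n = [1.960 × √(2 × 0.69 × 0.31) + 0.842 × √(0.65 × 0.35 + 0.73 × 0.27)]² / 0.08² = 523.5, so 524 per group. The stated figure is reproduced.

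**Inputs for the second-letter contrast**
- From the SAP: 4,000 women per arm, so 8,000 vs 8,000 in the pooled contrast. Bonferroni over the two secondary contrasts gives 0.05 / 2 = 2.5% each.
- Assumed, because the SAP gives no values: first-letter attendance f = 45-65%; response to an open second letter q = 10-25%; gain e from a timed second letter = 3, 5 or 8 points. Supplementary Table 1 shows service uptake of 42-67%, but that is total uptake and only a guide to f. The 8 points is the SAP's general timed-vs-open effect, not one stated for second letters.
- Simplifications: two-proportion normal approximation, the same f in both groups, no clustering.

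**Dilution.** On all invited women the rates are f + (1 − f)q and f + (1 − f)(q + e). Their difference is (1 − f)e. For f from 65% to 45%, 8 points becomes 2.8 to 4.4 points and 3 points becomes 1.05 to 1.65 points.

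**One case in full: f = 60%, q = 15%, e = 5 points**
- All invited: 0.60 + 0.40 × 0.15 = 66.0% vs 0.60 + 0.40 × 0.20 = 68.0%, IRR 1.03. SE = √(2 × 0.67 × 0.33 / 8,000) = 0.00744; z = 0.020 / 0.00744 = 2.69. Power = Φ(2.69 − 2.24) = 67%.
- Non-attenders: 8,000 × 0.40 = 3,200 per group, 15% vs 20%, RR 1.33. SE = √(2 × 0.175 × 0.825 / 3,200) = 0.00950; z = 0.050 / 0.00950 = 5.26. Power = Φ(5.26 − 2.24) = 99.9%.
- Relative information: (2.69 / 5.26)² = 0.26.

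Algebraically this ratio is close to the mean response among non-attenders divided by mean overall attendance, here 0.175 / 0.67 = 0.26. Over the assumed range it runs from 0.16 to 0.47, so 53% to 84% of the information is lost.

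**Power of the pooled contrast at 2.5%, all invited vs non-attenders**

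| Gain among non-attenders | f = 60%, q = 15% | f = 45-65%, q = 10-25% |
| --- | --- | --- |
| 3 points | 26% vs 84% | 21-45% vs 62-99% |
| 5 points | 67% vs 99.9% | 56-91% vs 97-100% |
| 8 points | 98% vs nearly 100% | 95-100% vs about 100% |

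A second illustration, f = 55% with responses of 10% vs 14%: all invited 59.5% vs 61.3%, IRR 1.03, power 53% at 2.5% (64% at 5%). Among non-attenders the ratio is 1.40, with power over 99%.

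**Smallest effect with 80% power at 2.5%, all invited.** About 2.2 to 2.4 points overall, which is about 4 to 6 points among non-attenders for f of 45% to 60%.

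**Single pairs at 5% (TT vs TO or OT vs OO, 4,000 per arm; f = 60%, q = 15%).** On all invited women, power is 21%, 48% and 86% for gains of 3, 5 and 8 points. Among non-attenders (1,600 per arm) it is 63%, 96% and over 99.9%.

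**The case against.** The strongest defence is that the planned contrast answers the stated question. The SAP's Objectives ask how combinations of timed and open invitations affect attendance in the programme, and comparing whole arms as allocated does exactly that. The Introduction says who gets a second letter; it does not commit the SAP to an effect confined to those women. This stands. A reader might infer that the all-invited contrast is wrong, but the document does not support that.

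A reader might also infer that most of the power is lost. That does not hold in general. At an 8-point gain, the only timed-vs-open effect the SAP mentions, pooled power on all invited women is still about 95% or more. It is at gains of about 3 points that the larger part goes, and every rate behind these figures is assumed. Nor does the SAP say that a non-significant second-letter result will be read as no effect; it asks for effect sizes with confidence intervals.

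The restricted analysis also conditions on something that happens after allocation. For open invitations the reference date is only a holding-clinic date, and the supplementary methods note that women may attend before it. Some women rebook and are neither plain attenders nor plain non-attenders. The Data dictionary has no field for when a second letter fell due. Comparability further assumes that nobody acts on the second-letter type before the first-letter outcome is known; the SAP describes no such mechanism, although parity can be read from the identifiers. These points shape the definition of the set. They do not rule out the analysis, because within a first-letter type a set fixed by attendance up to the first date does not depend on second-letter allocation under that assumption.

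**Conclusion.** This is a worthwhile, inexpensive improvement and not an error. The all-invited contrast is valid and should be kept. What the plan lacks is an estimate among the women to whom the second letter applies. Without it, more than half of the information on that effect is lost throughout the assumed range. The dilution by (1 − f) follows from the SAP's own design. How much power it costs does not, because it depends on f, q and e: severe at about 3 points, moderate at 5, slight at 8.

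The non-attender figures treat everyone who has not attended by the first date as open to the second letter. Women who had already rebooked will be in that set without needing one, so the realised gain in precision may be somewhat smaller.

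**What to change.** Add to Secondary analysis a supplementary comparison of allocated timed vs open second letter.
- **Set:** women who had not attended by the first offered date, or by the holding-clinic date for open first letters, whatever letter was actually printed.
- **Rebooking:** state in advance how women who rebooked before that date are handled, identically in both second-letter groups. Keeping them in the set is the simplest rule that does not depend on the second-letter arm.
- **Model:** stratify by first-letter type (TT vs TO, OT vs OO, then combined), since the first letter can change who becomes a non-attender. Use the same 90-day endpoint.
- **Reporting:** show the estimate with its 95% CI beside the all-invited IRR in Table 5, labelled supplementary and outside the fixed testing order.

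The cost is one definition, one extra model and two or three table rows. Allocation, appointment date, screening date, attendance and letter fields are already in the Data dictionary. Enter the analysis, with its date, in the List of changes to the Statistical Analysis Plan, so that readers can see whether it was added before or after the results were known.
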